**Methods and analysis:**

In this randomized, single-blinded, and placebo-controlled study, a total of 88 patients with depression in Parkinson’s disease (DPD) will be randomly allocated to either an acupuncture group or a control group in parallel in a 1:1 allocation ratio. Each group will receive 30 min acupuncture treatments or sham acupuncture treatments, 3 times a week, for 12 weeks, followed by a 36-week follow-up period. The primary outcome is the response rate of the Hamilton Depression Rating Scale-17 at 12 weeks. Data will be collected at baseline, at the end of the 12-week treatment period, and during the 12-week and 36-week follow-up.

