##### Primary indicator

The response rate (The response rate, defined as the proportion of total scores that decreased by at least 50% compared with baseline statistics) of HAMD-17 (at week 12).

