##### Secondary indicator

The change from baseline in resting-state fMRI (at week 12). The response rate of HAMD-17 (at weeks 24, and 48). The changes from baseline in UPDRS-III and PDQ-39 (at weeks 12, 24, and 48). The response rate of QIDS-SR, and the change from baseline in PDQ-39 (at weeks 12, 24, and 48). The proportion of patients with progression≥0.5 grades compared to the baseline of H–Y staging (at week 48).

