### Statistical analysis

#### Clinical data analysis

Statistical analysis will be conducted utilizing SPSS 20.0 (IBM Corporation, Armonk, NY, United States), a software package to analyze statistical data. Statistical significance was determined at the 0.05 level (two-tailed). The intention-to-treat (ITT) analysis will be employed as the primary analysis for all patients, and missing data were filled in using the last observation carried forward (LOCF). A supplementary analysis will be conducted using the adherence protocol analysis (PP).

The categorical data will be described using frequencies and percentages. The proportion of patients with progression ≥0.5 grades compared to the baseline of H–Y staging, and adverse events were analyzed using the chi-squared test. The initial step in the analysis of continuous data is to assess their normality. The data are described using mean ± standard deviation or median (interquartile range). Within-group comparisons are conducted using either paired *t*-tests or Wilcoxon signed-rank tests, while between-group comparisons are carried out using independent samples *t*-tests or Mann–Whitney *U* tests. HAMD-17, QIDS-SR, UPDRS-III, and PDQ-39 were analyzed using either repeated-measures ANOVA or a generalized linear mixed model based on repeated measurements.

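### Continuous secondary outcomes have several possible analyses, no rule for choosing between them and no stated baseline adjustment, which costs precision that a single baseline-adjusted model would recover

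*Protocol article*

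**What the plan says.** The Clinical data analysis section of the Protocol article makes two separate statements about continuous data.

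- It opens with a distributional check: "The initial step in the analysis of continuous data is to assess their normality". After the choice of summary statistics and the within-group paired tests, it says that "between-group comparisons are carried out using independent samples *t*-tests or Mann–Whitney *U* tests".
- It then names the scales: "HAMD-17, QIDS-SR, UPDRS-III, and PDQ-39 were analyzed using either repeated-measures ANOVA or a generalized linear mixed model based on repeated measurements".

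The section does not say which of the two families is the between-arm analysis of a given outcome, what decides between the two repeated-measures options, or whether any model contains the baseline score.

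The Secondary indicator section defines the continuous clinical endpoints as changes, and PDQ-39 appears there twice: "The changes from baseline in UPDRS-III and PDQ-39 (at weeks 12, 24, and 48". HAMD-17 and QIDS-SR enter the endpoint lists only as response rates. Their scores appear in the repeated-measures sentence, so those score analyses are supportive. Table 1 schedules all four scales at weeks 0, 12, 24 and 48, so the baseline value is available for each.

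**The concern.** Three features of the text cause difficulty together.

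1. **Data-dependent choice.** The natural reading is that the normality check selects the t or the rank test. The two do not estimate the same thing. A t-test concerns a difference in means, and a Mann–Whitney test in general does not. The quantity reported for UPDRS-III or PDQ-39 would then depend on the observed data.
2. **Several admissible methods.** On the text as it stands, each of these outcomes could be reported from a t-test, a rank test, a repeated-measures ANOVA or a mixed model. That leaves room for selective reporting, even if none is intended. Within-group tests are listed beside them with no note that they do not compare the arms.
3. **Lost precision.** No method is stated to adjust for baseline. Subtracting baseline is not the same as adjusting for it, and with 44 patients per arm the difference is worth having.

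At stake are the width of the confidence intervals and the credibility of the continuous secondary results, including the motor and quality-of-life findings. The trial's main test is not at stake.

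**Working it through.** **Inputs.** 44 patients per arm (Sample size calculation); two-sided 0.05 (Clinical data analysis); visits at weeks 0, 12, 24 and 48 (Table 1). The baseline-to-follow-up correlation r is not in the document. It is assumed, with a range of 0.3 to 0.7. Equal SDs at each visit are also assumed. The plan gives no precision or power figure for any continuous outcome, so there is no stated figure to reproduce.

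**Step 1: variance of the treatment difference at one visit.** In units of the score's SD² (common factor 2/n omitted; large-sample formulas):

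- follow-up score alone: 1
- change score: 2(1 − r)
- baseline-adjusted (ANCOVA): 1 − r²

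The ratio of ANCOVA to change score is (1 − r²)/[2(1 − r)] = (1 + r)/2. The ratio of ANCOVA to follow-up score is 1 − r².

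| r (assumed) | Change | ANCOVA | Saving vs change | Saving vs follow-up |
|---|---|---|---|---|
| 0.3 | 1.40 | 0.91 | 35% | 9% |
| 0.5 | 1.00 | 0.75 | 25% | 25% |
| 0.7 | 0.60 | 0.51 | 15% | 49% |

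Both ratios are below 1 for every r strictly between 0 and 1. The assumption sets the size of the gain, not its direction.

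**Step 2: what this means at 44 per arm.** The difference detectable with 80% power is (1.960 + 0.842) × √(2/44) × √(variance factor) = 0.597 × √(variance factor), in SD units.

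| r | Follow-up | Change | ANCOVA |
|---|---|---|---|
| 0.3 | 0.597 | 0.707 | 0.570 |
| 0.5 | 0.597 | 0.597 | 0.517 |
| 0.7 | 0.597 | 0.463 | 0.427 |

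**Step 3: chance imbalance.** The baseline difference between arms has standard error √(2/44) = 0.21 SD. A difference beyond 0.3 SD in either direction (z = 0.3/0.213 = 1.41) arises in about 16% of trials. Given an imbalance d, a follow-up comparison is shifted by r·d and a change-score comparison by (r − 1)·d. With d = 0.3 and r = 0.5 these are +0.15 and −0.15 SD. Baseline adjustment removes both shifts.

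**Step 4: repeated-measures ANOVA, if baseline is one of the four time levels.** Take a constant effect δ at the three later visits and none at baseline, with compound symmetry.

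- Group main effect: it estimates (0 + δ + δ + δ)/4 = 0.75δ. Rescaled to δ, its variance is [(1 + 3r)/4]/0.75².
- Contrast of the mean of the later visits minus baseline (interaction type): variance (1 + 2r)/3 + 1 − 2r.
- Baseline-adjusted mean of the later visits: variance (1 + 2r)/3 − r².

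At r = 0.5 these are 0.625/0.5625 = 1.111, then 0.667, then 0.417. The adjusted analysis has 0.417/1.111 = 0.38 of the main-effect variance and 0.417/0.667 = 0.63 of the contrast variance. At r = 0.3 the two ratios are 0.53 and 0.48; at r = 0.7 they are 0.23 and 0.78.

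**The case against.** The strongest reply has four parts.

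- **Baseline is not ignored.** A reader might infer from the two-sample tests that the plan throws baseline away. It does not: the UPDRS-III and PDQ-39 endpoints are changes, and an unadjusted change-score comparison in a randomised trial is valid. This stands. What remains is inefficiency, together with the residual shift of (r − 1)·d in step 3, because a change score over-corrects when r is below 1.
- **The mixed model could carry baseline, and an article may leave model terms to the SAP.** This stands in part. Silence on covariates alone would be no finding. But the article does fix something: it states a normality check, names unadjusted two-sample tests, and offers two repeated-measures methods without a rule for choosing.
- **The generic tests may not apply to these scales.** The sentence naming the four scales may govern them, with the t and rank tests kept for other continuous data. The text also never says outright that the normality check picks the test. Both readings are open. On the narrower one, the comparison with change-score tests does not apply, but the unresolved choice between ANOVA and mixed model, with no stated baseline term, does.
- **The dilution to 3/4 is conditional.** A reader might take it as a property of the plan. It needs baseline as a time level, the group main effect as the test, and a constant effect from week 12 to week 48. The article states none of these, and a group-by-time test is not diluted in this way.

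A reader might also infer a loss for the whole trial, since 25% less variance at r = 0.5 corresponds to 88/0.75 = 117 patients. That figure describes one change-score comparison at one assumed correlation. The primary endpoint is binary, "defined as the proportion of total scores that decreased by at least 50% compared with baseline statistics", and the sample size of 88 was set on it.

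**Conclusion.** The point holds for the continuous secondary outcomes (UPDRS-III and PDQ-39 changes) and for the supportive HAMD-17 and QIDS-SR score analyses. The plan leaves several methods open without a rule and names no baseline covariate. Relative to a change-score t-test, baseline adjustment would reduce variance by 35%, 25% or 15% at assumed correlations of 0.3, 0.5 or 0.7, and it would remove the effect of chance imbalance. These sizes rest on correlations that the article does not give and on equal SDs over time. The direction does not depend on the value chosen between 0 and 1. The shrinkage to 3/4 is a further risk only under the conditions named above. The primary comparison and the sample size are unchanged. This is an improvement that should be made, not a flaw that invalidates the trial.

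**What to change.** Replace the list of alternatives with one named model for each continuous outcome:

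- A mixed model for repeated measures on weeks 12, 24 and 48, with treatment, visit, treatment-by-visit, baseline score and baseline-by-visit. Baseline enters as a covariate, not as a time level.
- Fit it to the observed data. The section's last-observation-carried-forward rule should be stated not to apply to these models, since the fill-in would undo the model's own handling of missing visits.
- Report the adjusted between-arm difference with its 95% CI at each visit.
- Remove the normality check as a decision rule. Keep rank-based tests as sensitivity analyses, specified in advance.
- Label within-group paired tests as descriptive.

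The cost is analysis wording only. Baseline is already collected, and no visit, measurement or patient is added. The article reports that recruitment is still under way, so the change can be recorded as an amendment before the data are analysed.

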#### Image data analysis

All scans will undergo qualitative review by two radiologists to screen for potential brain lesions or structural abnormalities. The data processing is based on the MATLAB 2014a platform and is carried out using DPARSF V2.3. Using DPARSF V2.3, SPM12, and REST V1.8 for seed-based functional connectivity analysis. Using FSL 4.1 MELODIC ICA for independent component analysis. Using REST V1.8 for the Regional homogeneity method (ReHo). Utilizing DPARSF V2.3, SPM12, and REST V1.8 for Fractional Amplitude of low-frequency fluctuation (fALFF).

### Progress of research

The subject is currently recruiting patients continuously, and patients have been enrolled for regular interventions and follow-ups as per the trial design.

## Discussion

The principal objectives of this study are to evaluate the clinical efficacy and safety of acupuncture in the treatment of DPD and to investigate its mechanisms of neural regulation. The results of these studies will contribute to the establishment of a therapeutic program for effective and safe acupuncture intervention in DPD.

Depression is a common occurrence in early PD and persists throughout all stages, significantly impacting patients’ quality of life (40). The development of new therapeutic approaches to treat DPD is essential to improve the quality of life of DPD patients (41). This study was conducted following the academic experience of a renowned Chinese physician, [name], in treating PD. This study was a randomized, evaluator-blinded, sham acupuncture placebo-controlled trial to assess the efficacy and safety of acupuncture intervention for early mild-to-moderate DPD.

The present study has several innovative strengths. First, to the best of our knowledge, this study represents the first randomized controlled trial of acupuncture treatment for patients with early PD (H–Y staging ≤ grade 2.5) and mild-to-moderate depression, based on the internationally recognized Hoehn–Yahr staging criteria for PD. This study addresses the shortcomings of previous acupuncture research by separating DPD patients based on the severity of their condition. It investigates the potential benefits of early acupuncture intervention in DPD to determine if it can effectively delay the progression of PD during mid to long-term follow-up.

Secondly, this study selected scale and questionnaires and a combination of brain fMRI technology as the efficacy evaluation indicators. This study included fMRI data collection to explore the objective mechanism of acupuncture for early Parkinson’s disease with mild to moderate depression. Recent neuroimaging studies have begun to reveal the central mechanism of DPD (42–44), but the mechanism of acupuncture interventions to regulate the central nervous system remains is still unclear. The present study provides a foundation for future research on the central mechanisms of acupuncture treatment.

One potential limitation of this study is that, due to the practicalities of acupuncture treatment, blinding for acupuncturists cannot be implemented. A further limitation of this study is that we were unable to control medication use. To address this limitation, we had a professional physician conduct a systematic specialty assessment before enrolling patients. It was anticipated that no routine medication adjustments would be necessary for the duration of the next 3 months.
